**Specific objectives**

To assess the effect of 40 mg of rupatadine in reduction of the incidence of DHF

- To determine the effect of 40 mg of rupatadine on reduction of incidence of complications associated with DHF such as acute liver failure, hepatitis, the need for colloids, significant bleeding manifestations
- To determine if rupatadine reduces the duration of post illness fatigue and sleep disturbances

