**Secondary end point**

a. Reduction in complications such as liver failure with use of rupatadine. Liver failure will be diagnosed based on the following criteria. All of the 3 following criteria should be present (16).

- Absence of any previously known liver disease
- A prolonged prothrombin time of 4-6 seconds or more
- A INR of >1.5

b. Reduction in development of shock: Shock will be defined as a pulse pressure of ≤20 mmHg or a drop in the systolic blood pressure of 30mmHg or more

c. Reduction in need of colloids: use of dextran will be considered as the patient having significant fluid leakage as per National Guidelines

d. Reduction in need of blood transfusion/s: as per National Guidelines. Use of even 1 blood transfusion will be considered as the patient having significant fluid leakage

e. Reduction in duration of the illness. The first day of the illness will be defined as the day in which the patient developed fever. The day of recovery will be defined when **all** of the following 3 criteria are fulfilled:

- Patient afebrile for 24 hours
- Platelet counts of >50,000 cells/mm^3^ or a rise of 20% from the lowest value
- Return of the haematocrit to the patients baseline

f. Reduction in sleep disturbances: a reduction in sleep disturbances will be assessed by an eight point scoring system, known as the sleep condition indicator (17). This score assessed, difficulty in falling asleep, waking up in the night, quality of sleep, any effect of poor sleep in concentration, relationships, productivity and general wellbeing. The maximum score attainable is 32 and higher scores indicate better sleep quality.

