Interviews carried out on group of 15 patients revealed that reduction of fever, headache, body aches and return of appetite were important parameters for them. In addition, absence of post illness sleep disturbances and fatigue were also listed as important parameters by the patients. Therefore, we will record and measure these parameters in the daily assessments and also during follow up visits and telephone interviews.

A serial number will be used to identify the patient and the patient data will be entered in a data base where only the patient serial number will be used. Disease severity will be classified according to the 2011 WHO criteria (15).

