**Patient follow up**

All patients will be closely monitored during the trial as they will have to visit the study site (OPD) daily for assessment and for blood tests (FBC) as standard management of patients with dengue infection. 4ml of blood will be taken at the OPD for FBCs which are done at the hospital (NIID) as standard management of patients with dengue. All patients will attend daily, and assessed for presence of dengue warning signs and the blood pressure and pulse rate will be recorded. During the visits we will find out the day the patient recovers from illness as defined by the following criteria.

Day of recovery is defined when **all three** criteria below are fulfilled:

-Patient afebrile for 24 hours

-Platelet counts of >50,000 cells/mm^3^ or a rise of 20% from the lowest value

-Return of the haematocrit to the patient’s baselineIf the patient need to attend any OPD visits after the day of recovery, they will be paid Rs. 500 as reimbursement for travel. In each visit the patients will be assessed and monitored in an identical manner.

They will be asked to come 14 days after the onset of illness and the patients general wellbeing will be assessed by patient reported outcome measures including presence of any sleep disturbances (Annexure 3). At the 14 day follow up visit, a blood sample will be taken (4ml) and will be assessed for the presence of dengue IgM and IgG specific antibodies at the Centre for Dengue Research (CDR), University of Sri Jayewardenapura.

The patient will also be contacted 30 days after the onset of illness, by phone to assess the general wellbeing and presence of any sleep disturbances. At the follow up an interviewer administered questionnaire will be used to find out the post viral fatigue and sleep disturbances as previously used in similar studies (17-19). The modified fatigue scale has been previously used to evaluate post viral fatigue following West Nile virus infection (19), which is a viral infection similar to dengue. A fatigue questionnaire has been previously used to evaluate fatigue following dengue infection(18). Before administering these questionnaires to patients in this study (annexure 1), we will validate both questionnaires in this country by translating both to Sinhalese and Tamil.

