**Blood samples**: 4ml of blood will be obtained at the time of recruitment when the patient is being bled as per routine management of patients with dengue infection and again 14 days later to determine if the patient has primary or secondary dengue. Dengue NS1 will be performed at the OPD itself for with the initial blood sample and dengue virus serotype will be done at the CDR. The antibody testing will be done with the second blood sample at the CDR.

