## 8.6 Subsequent Visits

Once the patients are recruited they will be asked to visit the OPD daily for assessment as per National Dengue Management guidelines. During these visits, a detailed medical history regaring vomiting, appetite, how they feel (patient based score), presence of abdominal pain will be recorded. A detailed medical examination will be done and the temperature, heart rate, blood pressure, presence of hepatomegaly or pleural effusions or ascites will be recorded. After examination they will have a FBC done at the hospital and they will be sent home once they are assessed along with the report.

Each patient will be asked to come for 5 visits during acute illness and again 14 days after the onset of illness. The patients will be contacted by phone, 30 days after the onset of illness and a questionnaire will be administered (see follow up described above for details).

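### No sleep score is scheduled before the first dose, so the sleep comparison loses precision and cannot tell long-standing poor sleep from disturbance after dengue (low priority)

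*Protocol*

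**What the plan says.** Protocol, Secondary end point, item f: "a reduction in sleep disturbances will be assessed by an eight point scoring system, known as the sleep condition indicator (17". On scaling it adds: "The maximum score attainable is 32 and higher scores indicate better sleep quality". The item names neither a baseline nor a time point. Under Specific objectives the related aim reads: "To determine if rupatadine reduces the duration of post illness fatigue and sleep disturbances".

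On timing, the Protocol speaks in three places.

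- Trial Design, after listing what interviewed patients valued, including absence of sleep disturbance and fatigue after the illness: "Therefore, we will record and measure these parameters in the daily assessments and also during follow up visits and telephone interviews".
- Patient follow up: "They will be asked to come 14 days after the onset of illness and the patients general wellbeing will be assessed". That visit is "assessed by patient reported outcome measures including presence of any sleep disturbances (Annexure 3". A phone contact at illness day 30 covers sleep again.
- 8.5 Base line assessment lists history, co-morbidity, examination and a blood count. 8.6 Subsequent Visits lists "vomiting, appetite, how they feel (patient based score), presence of abdominal pain will be recorded", then examination and a blood count. Neither list has a sleep item, and 8.2 Screening and Eligibility Assessment has none either.

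Description of Statistical Methods plans ANCOVA for secondary endpoints where applicable, without naming covariates. It also plans a supplementary repeated measures analysis, and a standardised mean difference built on improvement in each arm.

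**The concern.** Treatment starts on the day of recruitment, so a pre-treatment sleep value can only come from the recruitment visit. If it is not asked there, no later document can supply it prospectively. An analysis plan can choose a model or a time point, but it cannot create a value that was never collected.

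Three things follow. The follow-up comparison carries all the between-patient variation in habitual sleep. A patient who has slept badly for years scores the same as one whose sleep worsened after dengue, although the objective concerns disturbance after the illness. And the planned ANCOVA has no baseline sleep covariate; if improvement in the effect-size formula means change, that formula has no starting value for sleep either.

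**Working it through.** **Where a sleep assessment is placed**

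| Section | Timing | Sleep item |
|---|---|---|
| 8.2 and 8.5 | recruitment | none listed |
| 8.6 | daily visits | none listed |
| Trial Design | daily, follow-up and phone | sleep disturbance promised; score not named, nothing said about before the first dose |
| Patient follow up | illness days 14 and 30 | yes |

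The promise of daily recording and the listed visit contents therefore do not match, and even the promise does not amount to a pre-treatment score.

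**Inputs.** The Protocol gives no SD, target difference or power for sleep, so there is no stated figure to reproduce.

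- Number per arm: 140 (Synopsis). With the 10% dropout in The Number of Participants, 140 × 0.9 = 126. The Protocol also gives a total of 262 (section 8.4) and 280 per group (The Number of Participants). The proportional gain below does not depend on which is used.
- Significance level: 0.05 (Protocol); two-sided is assumed.
- Power: 80%, assumed.
- r, the correlation of baseline with follow-up score: 0.3 to 0.7, assumed.

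**Formulas**

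- Variance of the adjusted treatment effect, relative to unadjusted: 1 − r².
- Detectable difference in SD units: (1.960 + 0.842) × √(2/n) × √(1 − r²).
- Without a baseline at n = 126: 2.802 × √(2/126) = 2.802 × 0.1260 = 0.353 SD.

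| r | Variance left | Variance cut | Detectable difference, n = 126 | Detectable difference, n = 140 | Power for 0.35 SD, n = 126 |
|---|---|---|---|---|---|
| no baseline | 1.00 | 0 | 0.353 | 0.335 | 79% |
| 0.3 | 0.91 | 9% | 0.337 | 0.319 | 83% |
| 0.5 | 0.75 | 25% | 0.306 | 0.290 | 89% |
| 0.7 | 0.51 | 49% | 0.252 | 0.239 | 97% |

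Expressed as sample size, 126 per arm with adjustment does the work of 126/0.91 = 138, 126/0.75 = 168 or 126/0.51 = 247 per arm without it.

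**Bias check.** The chance difference between arms in usual sleep has expectation zero and standard error √(2/126) = 0.126 SD, with 95% limits of about ±0.25 SD. It adds noise, not systematic error.

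**The case against.** The strongest reply is that the baseline may exist. Patient follow up cites Annexure 1 for the questionnaires, and Trial Design makes Annexure 1 the outpatient data form. A sleep item could therefore sit on the form used at recruitment. Nor is the list in 8.6 clearly exhaustive: it omits headache and body aches, which Trial Design also promises to record daily. This stands as a limit on certainty. It does not show that the score is taken before the first dose, and it leaves the sections to be reconciled.

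The reply on size also stands in part. No figure in the Protocol supports r of 0.5 or more for a febrile patient's recall of usual sleep, and at 0.3 the gain is small.

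A reader might infer four stronger points, which the documents do not support.

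- *That no reduction in sleep disturbance can be shown.* The same word introduces shock, colloid use and transfusion, where it means rupatadine against placebo. A between-arm difference at follow-up remains estimable; only change within a patient is not.
- *That prior poor sleep biases the result.* Randomisation balances it in expectation.
- *That having two follow-up times without a named one is a fault, or that day 30 must decide.* An analysis plan that is not shown may settle this, and the Protocol's repeated measures analysis could use both times. Testing each at 0.05 gives 1 − 0.95² = 9.75% only if the two tests were independent, which two scores from one patient are unlikely to be. Nothing in the Protocol favours day 30 over day 14.
- *That the sleep visit is misdated.* The paragraph on Blood samples says "again 14 days later to determine if the patient has primary or secondary dengue", but it concerns serology. Patient follow up and 8.6 both count the visit from illness onset.

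**Conclusion.** The point holds in a limited form. No section shown schedules a pre-treatment sleep score, and Trial Design disagrees with 8.5 and 8.6 on whether sleep is recorded at the visits. The follow-up comparison stays valid. It is less precise than it could be, and harder to interpret as an effect on disturbance that arose after dengue.

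The loss ranges from slight to material: the detectable difference at 126 per arm is 0.353 SD without a baseline, against 0.337 SD at r = 0.3 and 0.252 SD at r = 0.7. This rests on an assumed r, a two-sided 5% test, 80% power, and annexures that do not already contain the item. Priority is low: one of six secondary endpoints is affected, and neither the primary endpoint nor safety is touched.

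**What to change.** - Add the sleep condition indicator to the recruitment interview in 8.5, before the first dose, worded to ask about usual sleep before the illness. A score for sleep during acute fever may relate only weakly to later sleep.
- Name that value as the ANCOVA covariate for the follow-up sleep score.
- Reconcile Trial Design with 8.5 and 8.6: either list sleep among the items recorded at the visits or withdraw the promise of daily recording. If Annexure 1 already carries a baseline sleep item, say so in 8.5.

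The cost is a few minutes of a questionnaire the trial already plans to translate and validate. The downsides are a small burden on a febrile patient and some recall error, which lowers r and so the gain. The change has to be made before enrolment, because patients already treated cannot give a pre-treatment answer.

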# TRIAL DESIGN

This study is a randomized, double blinded, placebo controlled trial. The efficacy of the drug will be measured by how well it will be able to it reduce the proportion of patients who develop DHF. As secondary endpoints we hope to evaluate if it reduces the proportion of patients requiring hospital admission and also complications associated with dengue.

**Selection of patients**: Patients, who are suspected to be having a dengue infection, will be tested for dengue NS1 antigen test. These tests will be done free of charge for all patients with suspected dengue infection at the OPDs of the respective hospital. The patients who are confirmed to be having acute dengue infection and who fulfil the inclusion criteria and who do not have the exclusion criteria will be approached by a member of the team of investigators or by a medical officer of the unit who will be specially trained in obtaining informed written consent.

At the initial visit they will be assessed for the presence of dengue warning signs, their blood pressure and pulse rate recorded and a base line FBC done. They will be advised to come to the OPD for daily assessments and will be asked to come sooner if they develop persistent vomiting, feeling faint or develop any bleeding manifestations. They will be asked not to take any other over the counter drugs apart from any drugs given from the hospital (paracetamol) as per standard management of dengue.

**Data collection:** An interviewer administered questionnaire will be used to record basic demographic details of the patient. In those who are only assessed in the OPD setting (those who do not require hospital admission), basic demographic details, any co-morbid illnesses (diabetes, hypertension, asthma and allergic rhinitis), clinical features along with the daily full blood counts (FBCs) will be recorded liver function tests (Annexure 1). If the patient is admitted to hospital, additional clinical data such as hepatomegaly, presence or absence of serous effusion and additional investigations such as liver function tests, which are routinely done as standard management of dengue will be recorded (Annexure 2).

Interviews carried out on group of 15 patients revealed that reduction of fever, headache, body aches and return of appetite were important parameters for them. In addition, absence of post illness sleep disturbances and fatigue were also listed as important parameters by the patients. Therefore, we will record and measure these parameters in the daily assessments and also during follow up visits and telephone interviews.

A serial number will be used to identify the patient and the patient data will be entered in a data base where only the patient serial number will be used. Disease severity will be classified according to the 2011 WHO criteria (15).

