# SYNOPSIS

| Trial Title | The efficacy of rupatadine in treating dengue: a randomised, double blinded, placebo controlled trial | |
| --- | --- | --- |
| Short title | Efficacy of rupatadine in dengue | |
| Clinical Phase | Phase 2 | |
| Trial Design | Randomised, double blinded, placebo controlled | |
| Trial Participants | Patients with dengue infection | |
| Planned Sample Size | 280 with 140 each in each study arm | |
| Treatment duration | 5 days | |
| Follow up duration | 30 days of illness | |
| Planned Trial Period | 1 year | |
|  | Objectives | Outcome Measures |
| Primary | To determine the proportions of dengue patients who develop DHF when treated with and without rupatadine | Therefore, the reduction of the proportion of individuals who develop fluid leakage (DHF) will be assessed.  Evidence of plasma leakage: evidence of plasma leakage considered as detection of free fluid in the abdomen or by the presence of a pleural effusion by USScan and/or by the presence of a rise in haematocrit of >20% of the baseline. |
| Secondary | Investigate whether rupatadine treatment leads to a. reduction in complications such as liver failure.  b. Reduction in development of shock:  c. Need of colloids:  d. Need of blood transfusion/s:  e. Duration of the illness.  f. Sleep disturbance | Liver function tests, blood clotting, colloid infusion volumes, blood transfusion volumes, length of acute illness, sleep scores. |
| Investigational Medicinal Product(s) | Rupatadine 40mg | |
| Formulation, Dose, Route of Administration | Four 10mg tablets of rupatadine to be given orally, and placebo | |

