The number of adverse events (AE) were similar in those on rupatadine 40mg and on the placebo and all AE completely resolved (Table 1). Two patients (2.98%) in the placebo group developed a SAE, namely acute liver failure. AE such as hepatitis (ALT>250U/L) was more frequent in those on the placebo as 6 (8.9%) patients developed hepatitis when compared to 3 (4.5%) on rupatadine 40mg. Severe thrombocytopenia (<5×10^9^/L) was seen in one patient in the placebo group. However, thromobocyotopenia and hepatitis are known features of dengue and therefore, unlikely to be due to drugs.

|  | Rupatadine 40mg  N=66 | Placebo  N=67 |
| --- | --- | --- |
| Abdominal pain (%) | 17 (25.7) | 21 (31.3) |
| Vomiting (%) | 21 (31.8) | 21 (31.3) |
| Diarrhoea (%) | 27 (40.9) | 24 (35.8) |
| Hepatitis (%) (ALT>250/L) | 3 (4.5) | 6 (8.9) |
| Low platelet counts  <20 ×10^9^/L (%)  20 to 50×10^9^/L (%) | 12 (18.2)  17 (25.7) | 14 (20.9)  21 (31.3) |
| High ALT (>200 U/L) (%) | 9 (13.6) | 12 (17.9) |
| High AST (>200 U/L) (%) | 14 (21.2) | 18 (26.9) |
| Low white cell count  (<1×10^9^/L) (%) | 0 (0) | 0 (0) |

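### The protocol contradicts itself on whether outpatients have liver function tests and schedules PT/INR for nobody, so liver outcomes may be found mainly in admitted patients and the arm comparison can be biased

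*Protocol*

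**What the plan says.** **What is to be compared.** Secondary end point (a) is liver failure. All three of its criteria must be present: no previously known liver disease, "A prolonged prothrombin time of 4-6 seconds or more", and an INR above 1.5. The Specific objectives extend the comparison to "complications associated with DHF such as acute liver failure, hepatitis, the need for colloids, significant bleeding manifestations". The Synopsis gives the secondary outcome measures as "Liver function tests, blood clotting, colloid infusion volumes, blood transfusion volumes, length of acute illness, sleep scores", without saying when they are taken or in which patients.

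**What is to be collected.** Under Trial Design, Data collection, the sentence on patients managed only in the OPD reads "clinical features along with the daily full blood counts (FBCs) will be recorded liver function tests (Annexure 1". The wording is damaged, but it names liver function tests. The next sentence, on admitted patients, has "additional investigations such as liver function tests, which are routinely done as standard management of dengue will be recorded (Annexure 2". Under Patient follow up the daily sample is described thus: "4ml of blood will be taken at the OPD for FBCs which are done at the hospital (NIID) as standard management". Sections 8.2, 8.5 and 8.6 also name only a full blood count (FBC). The day-14 sample is for dengue antibodies.

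**PT and INR.** Outside the endpoint definition they appear only in the hepatic exclusion criterion, which is checked from the patient's account and clinical records.

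**The concern.** A laboratory-defined outcome can be compared between arms only if both arms are tested alike. If the visit descriptions are followed as written, outpatients have no liver function tests, admitted patients have whatever routine care orders, and PT/INR depends on a clinician choosing to request it.

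Admission is not a neutral gateway to testing. It happens after randomisation. The Primary Study Endpoints section says that anyone suspected of leakage is admitted, and Trial Design names fewer admissions as a hoped-for effect of the drug. If rupatadine lowers admission, fewer rupatadine patients are tested and fewer liver events are found, even if the drug does nothing to the liver.

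The adverse event system does not close the gap. Section 10.3 records events that the investigator observes or the participant reports, and an ALT rise that nobody measured is neither. The comparison is also likely to be cited: the Background already points to less hepatitis on rupatadine in the earlier trial.

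**Working it through.** The protocol states no figure on this point, so there is none to reproduce. The check has two parts.

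**1. Which section provides which test**

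| Protocol section | Patients | Liver function tests | PT/INR |
|---|---|---|---|
| Synopsis, outcome measures | not stated | named, no timing | blood clotting named, no timing |
| Secondary end point (a) | all | – | required by definition |
| Trial Design, Data collection, OPD sentence | OPD only | named (Annexure 1) | not named |
| Trial Design, Data collection, next sentence | admitted | additional, routine care (Annexure 2) | not named |
| Trial Design (initial visit), 8.2, 8.5 | all, at entry | not named; FBC only | not named |
| Patient follow up, 8.6 | OPD, daily | not named; FBC only | not named |
| Day-14 sample | all | not named; serology | not named |
| Exclusion Criteria | at entry | – | from history and records |

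Two results follow. The sections disagree on liver function tests in outpatients. No section schedules PT/INR, in either setting.

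**2. How large the bias could be**

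Inputs:
- True hepatitis rate r, equal in both arms: 6/67 = 8.96% (ALT above 250 on placebo in the earlier trial, Background).
- True liver failure rate, equal in both arms: 2/67 = 2.99% (same source).
- 140 patients per arm (Synopsis).
- Admission proportions a0 (placebo) and a1 (rupatadine). **The protocol gives none, so these are assumed.** The main pair, 42.8% and 23.5%, is borrowed from the placebo and rupatadine ascites proportions in Table 2 (9/21 and 4/17), on the reasoning that suspected leakage leads to admission. Other pairs show the range.

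*Detection only on admission, admission unrelated to the liver event.* The observed rate is r × a in each arm, so the apparent risk ratio is a1/a0, whatever the value of r.

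| Assumed admission, placebo vs rupatadine | Apparent risk ratio | Hepatitis cases seen, placebo vs rupatadine (12.5 true per arm) |
|---|---|---|
| 42.8% vs 23.5% | 0.55 | 5.4 vs 2.9 |
| 60% vs 40% | 0.67 | 7.5 vs 5.0 |
| 80% vs 60% | 0.75 | 10.0 vs 7.5 |
| 50% vs 50% | 1.00 | 6.3 vs 6.3 |

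First row: 0.235/0.428 = 0.55; 140 × 0.0896 × 0.428 = 5.4; 140 × 0.0896 × 0.235 = 2.9.

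*Some liver events are admitted in either arm.* Let s be the share of liver events that reach hospital regardless of treatment. Then the apparent risk ratio is [s + (1 − s)a1] / [s + (1 − s)a0]. With 42.8% and 23.5%:

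| s | 0 | 0.25 | 0.50 | 0.75 | 1 |
|---|---|---|---|---|---|
| Apparent risk ratio | 0.55 | 0.75 | 0.86 | 0.94 | 1.00 |

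For s = 0.5: (0.5 + 0.5 × 0.235)/(0.5 + 0.5 × 0.428) = 0.6175/0.714 = 0.86.

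*Chance of a false significant benefit* in the extreme case (s = 0, 42.8% vs 23.5%, two-sided 5%, so nominally 2.5% in the drug's favour). For hepatitis it is about 12% to 13% with the chi-square test (exact enumeration and normal approximation) and about 6% with Fisher's exact test. For liver failure, with 1.8 vs 1.0 expected cases, it is about 0.4% with Fisher's test, which the Statistics section names for small numbers. The distortion is therefore mainly in the estimate, and mainly for hepatitis.

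**The case against.** **Outpatients may be tested.** The OPD sentence in Data collection does name liver function tests and ties them to the OPD form. A reader might infer from the visit sections that liver events are seen only in admitted patients. The text does not support that: it contradicts itself, and Annexures 1 and 2 are not available to settle it. The objection stands against the word "only". It does not remove the contradiction, because the fragment gives no timing and no visit section follows it up. Nor does it touch PT/INR, which it does not mention.

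**Serious liver disease would reach hospital anyway.** Patients are assessed daily for warning signs, and section 8.6 records hepatomegaly at each visit. This is a good argument for overt liver failure: if s is close to 1, the bias vanishes. It is weak for hepatitis defined by an ALT threshold, since neither hepatomegaly nor warning signs substitute for the assay.

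**The inputs are borrowed.** The admission rates are assumptions. The hepatitis rate comes from patients enrolled at up to five days of illness, whereas this trial recruits earlier. Hepatitis is in the objectives but is not defined among the secondary end points. All of this is correct. The figures show how the mechanism scales and do not forecast the result.

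**Liver injury as the main risk of the drug.** A reader might infer this from "Two patients (2.98%) in the placebo group developed a SAE, namely acute liver failure". The documents do not support it. Both cases were on placebo, hepatitis was less frequent on rupatadine 40 mg (3/66 against 6/67), the Background attributes liver events to dengue, and it presents vascular leak and shock as the hallmark of severe disease.

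**Conclusion.** The point holds as an internal contradiction and a gap in measurement. The protocol disagrees with itself on liver function tests in outpatients, and it schedules PT/INR for no one although secondary end point (a) depends on it. Testing may therefore follow admission, and the liver comparison can be biased towards rupatadine.

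Under no true liver effect, the apparent risk ratio runs from 0.55 (detection only on admission, assumed admission 42.8% vs 23.5%) through about 0.86 (half of liver events admitted in either arm) to 1.00 (all admitted, or equal admission). Bias needs two conditions: admission must differ by arm, and liver events must go unmeasured outside hospital. Both are plausible for laboratory-defined hepatitis. The second is doubtful for overt liver failure. It would be too strong to say that a fall in admissions will look like liver protection; it can.

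This is more than a detail left to an analysis plan. The timing of blood tests is protocol content, and no analysis can recover values that were never measured.

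**What to change.** Reconcile the Synopsis, Specific objectives, Secondary end point (a), Data collection, Patient follow up and sections 8.5 and 8.6. State one set of assessment times for ALT/AST and PT/INR that applies to every randomised patient in both arms, whether or not admitted. Choose them from visits where blood is already drawn: recruitment, the daily acute visits and day 14. Base the between-arm liver analysis on those scheduled values, and list any additional routine-care results separately. Define hepatitis if it is to be compared.

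The cost is protocol wording, a modest laboratory bill for a few assays per patient, and a clotting tube at the chosen visits.

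If the sponsor does not do this, report liver failure and hepatitis descriptively as events detected under routine care, and make no between-arm efficacy claim from them. That costs nothing beyond the claim itself.
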